**3.5 Randomization and Interventions (if applicable)**

A randomized assignment will be placed in an envelope that will be opened by the intervention administrator during the participants’ first clinical site visit (Day 1 of the study). Until that time, the intervention administrator will be blinded to the randomized assignment until it is revealed to the participant. However, because of the “open disclosure” of placebo use, study assignments cannot be blinded to the intervention administrator or to the participant once the envelope is opened. To control bias, the intervention administrator will have limited contact with the participants after Day 1 with the exception of a brief “re-orientation” on Day 28 at the beginning of Period 2 .

On Day 28, participants originally assigned to Group2 will receive the OLP and be prescribed two placebo pills twice a day to take over the course of 3 weeks (21 days). The participants who were randomly assigned to Group1 will serve as the NO OLP observational controls over the course of 3 weeks (21 days).

Figure 2: Crossover Study Arms

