**Intervention: Placebo Orientation Meeting (Day 1 of Study / 1st Clinical Site Visit)**

At the beginning of the first clinical site visit (Day 1 of Study) the research specialist will acquire informed consent from the participant. Once the participant has provided his or her consent, the research specialist will review the four questionnaires with the participant, address any questions or concerns and ask the participant to complete each instrument. After reviewing the questionnaires for missing data, the research specialist will label each completed questionnaire with the appropriate study numeric identifiers and store the questionnaires in a secured unit for future analysis. The research specialist will then instruct the participant on how to use the ORAGENE® Discover (OMR-500) saliva collection test kit and a saliva sample will be collected, labeled with the appropriate study identifiers and stored in a secured unit for future analysis. The research specialist will schedule all 3 subsequent clinical site visits (Days 21, 29 and 49) and introduce the participant to the intervention administrator.

The intervention administrator will deliver a persuasive rationale for the OLP to the participant as part of the OLP Orientation on Day 1. The persuasive rationale (OLP orientation) is a critical component of this study and will be presented to participants in a way that fosters positive expectations, without deception, when a placebo is delivered. The script for the persuasive rationale includes dialogue that:

- Supports positive expectations and trust with an accurate description of what is known about placebo effects;
- Allows for contradictory thoughts including doubt and disbelief; and,
- Encourages adherence to the medical ritual of pill taking.

Four main discussion points will be included in *a priori* script that takes approximately 20 minutes to deliver (see Table1). The introduction will begin with a question:

- “Have you ever heard about placebo effect prior to our discussion on the phone?” followed by a natural give-and-take discussion.
- The practitioner will explain (or support the patient’s understanding) that “placebo pills are made of an inert substance, like sugar or starch, that has been shown in clinical studies to produce significant improvement in a variety of symptoms including fatigue and pain, through mind-body, self-healing processes that our bodies can naturally do.”

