The delivery of the persuasive rationale will be audio-recorded in all patients for use in establishing fidelity to treatment. Because of the importance of the interaction between the intervention administrator and the participant, all interactions will take place in the context of a warm, supportive and natural interaction. The importance of the no-treatment control group will also be discussed and questions will be answered. After the placebo orientation, the envelope with the randomized assignment will be opened and both the participant and the intervention administrator will learn which group the participant will join.

**Group1**: Participants assigned to Group1 will be given a pre-filled, twice-per-day weekly pill organizer. The intervention administrator will instruct Group1 to “take 2 pills in the morning with breakfast and two pills in the evening before bedtime.” The placebo pills will be blue and maroon gelatin capsules filled with non-absorbable Avicel® (Microcrystalline cellulose), a common inert excipient for pharmaceuticals. Prior to departing, the participant will ingest two of the placebo pills and be given a medication diary with instructions to record each time placebos are taken so that a pill count can be made.

**Group2**: Participants assigned to Group2 will be reassured that they will receive the OLP during Period 2 of the study. The intervention administrator will also reiterate the importance of the role of observational controls.

Parking tickets will be stamped and participants will be provided contact information for study team member and IRB should they have questions or concerns. They will be given a reminder card with their next appointments (Day 21, Day 29 and Day 49). They will also be told to expect a follow up telephone call from a study team member midway through Period 1 on or about Day 11. The estimated time for the first clinical site visit (Day 1) is 60 minutes.

**Mid-Point Check-In Call:** participant is called to check on condition. Calls lasts < 5 minutes.

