**End of Period 1 (Day 21 of Study / 2nd Clinical Site Visit**): Study participants will be instructed to return to the clinical site on Day 21 of the study. At that time, the research specialist will collect the medication diaries and address any questions or concerns. The research specialist will administer the 4 questionnaires that will be labeled with the appropriate study identifiers and stored in a secured unit for future analysis. Participants will be reminded of their next clinical site visits (Day 29 and Day 49) and parking tickets will be stamped. Once again, participants will be reminded of the value of their participation. The estimated time for the 2nd clinical site visit is 25 minutes.

**Beginning of Period 2 (Day 29 of the Study / 3rd Clinical Site Visit):** On Day 29, participants will return to the study site to begin Period 2 of the trial. The research specialist will review the 4 questionnaires with the participant, address any questions or concerns and ask the participant to complete each instrument. The research specialist will label each completed questionnaire with the appropriate study numeric identifiers and store the questionnaires in a secured unit for future analysis. The intervention administrator will meet with participants to explain procedures for Period 2.

**Group1** : participants will be informed that they are now the OC and the value of that role will be reiterated. They will be reminded of their next clinical site visit and told to expect a follow up call at some point (on or about Day 39). Parking tickets will be stamped and the participant will be provided a reminder of the next (and final) clinical site visit (Day 49 of the study).

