**Group2** : participants will be informed that they will now receive the OLP. The intervention administrator will re-present a brief version of the rationale for the OLP and remind participants of the 4 main points from the original orientation meeting. Participants will be encouraged to ask questions and discuss concerns. Participants assigned to Group2 will be given a pre-filled, twice-per-day weekly pill organizer. The intervention administrator will instruct Group2 to “take 2 pills in the morning with breakfast and two pills in the evening before bedtime.” The placebo pills will be blue and maroon gelatin capsules filled with non-absorbable Avicel (Microcrystalline cellulose), a common inert excipient for pharmaceuticals. Prior to departing, the participant will ingest two of the placebo pills and be given a diary with instructions to record each time placebos are taken so that a pill count can be made. They told to expect a follow up call at some point (on or about Day 39). Parking tickets will be stamped and the participant will be provided a reminder of the next (final) clinical site visit (Day 49).The estimated time for the Day 29 clinical site visit is 35 minutes.

**Mid-Point Check-In Call:** participant is called to check on condition. Calls lasts < 5 minutes.

**End of Period 2/End of Study (Day 49):** Study participants will return to the clinical site on Day 49 of the study. At that time, the research specialist will collect the medication diaries and address any questions or concerns. The research specialist will administer the remaining questionnaires and assure that all questionnaires are stored in a secured unit for future analysis. The intervention administrator will meet briefly with participants to thank them for their participation and to distribute cash incentives. Parking tickets will be stamped. The estimated time for this visit is 25 minutes.

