**Specific Aim 2:** We will test the hypothesis that an OLP intervention reduces symptoms severity of CRF and improves quality of life for CSs compared to an observational control. The primary analysis for this aim will consist of mixed models repeated measures analysis, such as repeated measures analysis of covariance. This will allow the investigators to properly test for the absence of a carryover effect as well as account for the fact that all patients will receive both treatments (i.e., this type of analysis allows each patient to serve as his/her own control).

**Supplementary Aim:** evaluates the presence or absence of the COMTVal18Met genotype as a correlate for improved fatigue conditions and quality of life. We will measure this using a logistic regression model to determine associations. In addition, we will calculate the odds ratio and corresponding 95% confidence intervals.

**Multiple Comparisons Tests (Post Hoc Test):** To account for multiple comparisons, we will apply a Bonferroni procedure and control the family-wise error rate at .05.

**Missing Data**: Data deemed missing at random (MAR) will be handled using multiple imputation techniques with the Bayesian based Markov-Chain Monte-Carlo (MCMC) method. In supplementary analysis, we will use independent t-tests and chi-square to compare completers versus dropouts.

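### The OLP-versus-control contrast differs in form between the two periods, so the combined Aim 2 estimate mixes two contrasts and period-end data cannot separate that difference from carryover

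*Protocol*

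**What the plan says.** Protocol 3.5, Placebo Orientation Meeting (Day 1), treats the rationale as part of the intervention: "The persuasive rationale (OLP orientation) is a critical component of this study". It is a "script that takes approximately 20 minutes to deliver". Every participant receives it ("The delivery of the persuasive rationale will be audio-recorded in all patients"), and allocation becomes known only later: "After the placebo orientation, the envelope with the randomized assignment will be opened". Group1 then gets pills and a diary. Group2 is assured of the OLP in Period 2.

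Protocol 3.5, Beginning of Period 2, places the four questionnaires first, with the research specialist. The intervention administrator meets participants afterwards. For Group2: "The intervention administrator will re-present a brief version of the rationale for the OLP and remind participants of the 4 main points", followed by pills and a diary. For Group1: "participants will be informed that they are now the OC and the value of that role will be reiterated". No rationale is described for Group1 at this visit. The opening of 3.5 limits the administrator's contact after Day 1 "with the exception of a brief “re-orientation” on Day 28 at the beginning of Period 2" and does not say which group receives that re-orientation.

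Protocol 3.7, Specific Aim 2, plans a mixed-model repeated-measures analysis. It is said to give a proper test that carryover is absent and to "account for the fact that all patients will receive both treatments". The power calculation in 3.7 rests on the Day 21 comparison alone.

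**The concern.** In Period 1 the two groups differ by pills, diary and known assignment, and both have heard the rationale the same day. In Period 2 they differ by the same items plus a renewed rationale in the OLP group only. Section 3.7 speaks of two treatments received by everyone and does not mention that the comparison changes.

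Two things follow. A combined estimate averages two contrasts that need not be equal. And in a two-period, two-sequence crossover, a treatment effect that varies by period enters the same contrast as carryover, so a test of one is also a test of the other. The trial is meant to supply effect sizes for a larger study (Protocol 1.0), so readers need to know which contrast a reported effect represents.

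**Working it through.** **The plan's own figure.** Inputs from 3.7: two-sided alpha 0.05, power 80%, effect size 0.64, two-sample t-test at Day 21. By normal approximation, n per group = 2(1.960 + 0.842)²/0.64² = 38.3, so 39. By the noncentral t distribution it is 39.3, so 40 per group and 80 in total, with 80.7% power at 40 per group. The stated 80 reproduces. It uses Period 1 only.

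**Exposure by group and period (Protocol 3.5).**

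| | OLP group | Control group |
| --- | --- | --- |
| Period 1 | Full rationale that day; pills and diary | Full rationale that day |
| Period 2 | Full rationale four weeks earlier; brief version that day; pills and diary | Full rationale four weeks earlier; told it is now the control |

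**Expected period-end means (Days 21 and 49), improvement counted as positive.** Let mu be the Period 1 control mean, pi the period effect, tau the Period 1 OLP effect, beta the net amount by which the OLP effect in Period 2 differs from tau, and lambda the benefit that Group1 carries into its control period.

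- Group1: mu + tau, then mu + pi + lambda
- Group2: mu, then mu + pi + tau + beta

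**Contrasts.**

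- Period 1, OLP minus control: tau
- Period 2, OLP minus control: tau + beta − lambda
- Combined (mean of the two): tau + (beta − lambda)/2
- Sequence contrast (Group1 total minus Group2 total): lambda − beta

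There are four cell means and five parameters. The design matrix has rank 4 with beta alone, rank 4 with lambda alone and still rank 4 with both. Beta and lambda are therefore not separately estimable from the period-end outcomes, whatever their size. For example, with tau = 0.64 and beta = lambda = 0.32, the sequence contrast is 0.32 − 0.32 = 0 although carryover exists.

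**Sign and size of beta.** The Protocol gives neither. Let r be what the renewed rationale adds and d what is lost because Group2's full rationale came four weeks before its pills. Then beta = r − d, which may be positive, zero or negative. Taking beta from −0.3 to +0.3 SD as an assumption and lambda = 0, the combined estimate shifts by beta/2:

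- |beta| = 0.1: 0.05 SD, 0.05/0.64 = 8%
- |beta| = 0.2: 0.10 SD, 0.10/0.64 = 16%
- |beta| = 0.3: 0.15 SD, 0.15/0.64 = 23%

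**How much a sequence test could show.** Section 3.7 does not name the form of its carryover test. As an illustration, take participant totals, 40 per group, no baseline adjustment and a between-period correlation rho of 0.3 to 0.7 (assumed). The standard error is sqrt[(2/40) × 2(1 + rho)], that is 0.361 SD at rho = 0.3 and 0.412 SD at rho = 0.7. For 80% power the net difference lambda − beta must be 2.80 × SE, about 1.01 to 1.16 SD. A net difference of 0.1 to 0.3 SD would be flagged in only about 6% to 13% of trials.

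**What the start-of-Period-2 questionnaires add.** In the visit text they precede the administrator meeting. A group difference there is not affected by the renewed rationale and can show carryover still present at that visit. Carryover acting at Day 49 stays mixed with beta unless it is tied by assumption to that earlier difference.

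**The case against.** The strongest reply is that the reminder may make the periods more alike. Group1 starts pills just after the full rationale. Without a reminder Group2 would start four weeks after it. Re-presenting the rationale keeps it close to the first pill in both OLP groups. This stands as an argument about direction: a reader might infer that the asymmetry inflates the Period 2 effect, and the Protocol does not support that, because r − d may have either sign. It does not make the contrasts equal, since the controls still differ in how recently they heard the rationale.

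A reader might also infer that carryover cannot be examined at all. That goes too far, given the questionnaires at the start of Period 2. The 6% to 13% figures belong to an illustrative test that the Protocol does not specify, and a baseline-adjusted model could behave differently.

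Model terms and by-period estimates may be left to an SAP, which is not at hand. Their absence is not an error. The asymmetric delivery and the assurance about the carryover test, however, are in the Protocol itself.

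It is tempting to ask that Group1 also hear the rationale again at the start of Period 2. That could prolong a persisting effect in participants who are off pills, so it is a trade-off on which designers may reasonably differ. The documents do not show that it is needed.

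Finally, the stakes are limited. The primary objective is feasibility and acceptability, and Aim 2 is secondary in a pilot. The sample size does not depend on Period 2.

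**Conclusion.** The point holds in a limited form. As written, the two periods estimate OLP contrasts that differ in form, and for Day 21 and Day 49 outcomes that difference cannot be separated from carryover. This is algebra and needs no assumed effect size. The assurance in 3.7 of a proper test for absence of carryover is therefore too strong.

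How far a combined estimate moves is unknown in size and sign: ±0.05 to ±0.15 SD if beta lies between 0.1 and 0.3 SD in absolute value and there is no carryover. Those values are assumptions. The conclusion also takes the detailed visit text at its word that only Group2 hears the rationale again. If the re-orientation in the opening of 3.5 was meant for both groups, the asymmetry would shrink or vanish.

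**What to change.** In Protocol 3.7, Specific Aim 2:

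- Report the OLP-minus-control effect separately for each period beside any combined estimate. Show the Period 1 (Day 21) contrast, on which the sample size rests, as the estimate free of both carryover and the renewed rationale.
- Describe the Period 2 contrast as OLP with renewed rationale versus neither.
- Use the group difference on the start-of-Period-2 questionnaires as the check for residual effect, noting that it speaks only to that visit.
- Replace the assurance about testing for carryover with a statement that the sequence term mixes carryover with a treatment-by-period difference.

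In 3.5, reconcile the opening text on the re-orientation, which is not limited to a group, with the visit text, which gives the rationale to Group2 only. The two also differ on the day (28 versus 29).

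The cost is wording and a few extra table rows, with no change to visits or staff. The downside is precision. A single-period contrast with 40 per group has a standard error of sqrt(2/40) = 0.224 SD without baseline adjustment. The combined estimate has sqrt[(2/40) × 2(1 − rho)]/2 = 0.132 to 0.087 SD for an assumed rho of 0.3 to 0.7. Keeping the combined estimate beside the by-period ones retains that gain for readers who accept its assumptions.

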**3.6 Measures**

To qualify for the study, CSs must have a self-assessed fatigue severity level of >4 on a 0-10 scale with 10 being “extremely severe fatigue”. In addition to demographics, 3-questions will be asked during the screening process that will help assess feasibility and acceptability. OLP treatment effect will be measured with 4 questionnaires administered to participants Day 1 (Baseline) Day 21, Day 28 and Day 49 (End of Study). We will also determine the presence of the COMTVal18Met genotype.

**3.6.1 Primary Study Aim Outcomes**

**Specific Aim 1** evaluates the feasibility of recruiting and enrolling CSs into an OLP and the acceptability by CSs of an OLP for the treatment of CRF. We propose to measure these two outcomes as follows:

- Feasibility: among eligible CSs who inquire about our study, we will calculate the proportion of those who, after completing the screening procedure, (1) sign the consent form, (2) decline to participate and (3) participate but drop out. We will gather qualitative information from CSs concerning their reasons for declining to participate or dropping out. We will also investigate whether the screening questions pertaining to outcome expectancy and credibility associate with study retention and/or placebo responses, as well as whether randomized assignment associates with retention.

During the screening process, prospective enrollees will be asked 3 questions that pertain to credibility belief, outcome expectancies, and acceptability of an OLP. The rationale for asking these questions is to assess the feasibility of an OLP study for CSs, and to assess whether the responses to credibility beliefs, outcome expectancy predict acceptability and subsequent placebo responses (which may have implications for selecting patients for future clinical trials).

- **Credibility Belief**: “Based on what I have said today, how logical does taking placebo pills to make help someone feel better seem to you?” Responses will range from 0 (makes no sense at all) to 10 (makes perfect sense).
- **Outcome Expectancy**: “At this point, how successful do you think this treatment will be in reducing your fatigue?” Responses are measured on a 0% to 100% scale.
- **Acceptability**: “Based on my description of the study, are you still interested in participating?” Responses will be “yes” or “no”, or “not sure”. Those who respond “not sure” will be given 48-hours to decide if they wish to participate and will receive a follow-up call.
- Acceptability will also be measured by
- Accrual Rate
- Retention Rate
- Placebo Pill Adherence Rate

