**Primary Objective**

**Specific Aim 1**: Assess the feasibility of an Open-Label Placebo (OLP) for treating CRF in cancer survivors (CSs).

Hypothesis 1: An OLP will be perceived by the majority of CSs screened as credible and acceptable and we will meet our enrollment, retention and adherence targets.

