**Screening**: During a telephone screening, prospective participants will be asked to rate their current fatigue severity (0=no fatigue; 10=extremely severe fatigue). Those who report moderate fatigue (4) and who meet the other inclusion criteria (see Section 3.4) will be told that they qualify for the study after information is verified in IMPACT. The participants will be informed that:

- They will receive “placebo pills” at some point during the study.
- In several studies, placebos have been found to be just as effective, if not more so, than many drugs being used to relieve pain, to treat depression, anxiety, sleeplessness and fatigue when used in placebo-controlled clinical trials.
- Current recommended CRF treatments have not demonstrated adequate effect for relieving CRF symptoms.
- Placebos have been tested and found to be effective for relieving fatigue and pain in patients with symptoms related to IBS and migraines.
- They will be reimbursed for parking expenses.
- They will receive up to $75.00 in the form of cash for participating in the study.

**Enrollment:** After we identify eligible participants and receive a positive indication of willingness to participate, we will ask them for demographic information during the screening call. As each participant is verified and enrolled into the study, he or she will be scheduled for a total of 4 clinical site visits. Once the participant is enrolled, we will mail all relevant measurement instruments, instructions and consent forms prior to the first scheduled clinical site visit or Day 1 of the study.

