**3.6.4 Primary Endpoint**

To evaluate the feasibility of recruiting and enrolling CSs into an OLP and the acceptability of CSs of an OLP for the treatment of CRF.

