**Statistical Analysis**

**Specific Aim 1:** We will evaluate the feasibility of recruiting and enrolling CSs into an OLP intervention.

Feasibility: among eligible CSs who inquire about our study, we will calculate the proportion of those who, after completing the screening procedure,

- sign the consent form;
- decline to participate;
- participate but drop out.

During the screening process, prospective enrollees will be asked 3 questions that pertain to credibility belief, outcome expectancies, and acceptability of an OLP. The rationale for asking these questions is to assess the feasibility of an OLP study for CSs, and whether credibility beliefs, outcome expectancy predict acceptability (which may have implications for selecting patients for future clinical trials). We will use an analysis of variance (ANOVA) to determine if credibility belief and/or outcome expectancy predicts acceptability.

- **Credibility Belief**: “Based on what I have said today, how logical does taking placebo pills to make help someone feel better seem to you?” Responses will range from 0 (makes no sense at all) to 10 (makes perfect sense).
- **Outcome Expectancy**: “At this point, how helpful do you think this treatment will be in reducing your fatigue?” Responses are measured on a 0% to 100% scale.
- **Acceptability**: “Based on my description of the study, are you still interested in participating?” Responses will be “yes” or “no”, or “not sure”. Those who respond “not sure” will be given 48-hours to decide if they wish to participate and will receive a follow-up call.

Acceptability: This will be determined proportionally by:

- **Accrual Rate**: baseline = 80 eligible participants
- **Retention Rate**: baseline = >75%
- **Adherence Rate**: placebo adherence by actual pill count and medication diary entries compared to an anticipated baseline rate of 100%.

For the analysis of acceptability, we will use a chi-square test, or Fisher’s exact test when the assumptions for the chi-square are not tenable. We will also apply log linear models if necessary to adjust for covariates.

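### The screening item labelled acceptability asks about joining the study, so it does not give a pill-specific share of those screened who find open-label placebo acceptable

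*Protocol*

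**What the plan says.** Under Primary Objective in Section 2.0, Hypothesis 1 states: "An OLP will be perceived by the majority of CSs screened as credible and acceptable". Section 3.6.1 names the outcome as "the acceptability by CSs of an OLP for the treatment of CRF", and Section 3.6.4 gives the primary endpoint in the same terms: "acceptability of CSs of an OLP for the treatment of CRF". In all three places the object is the treatment.

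Section 3.6.1 then describes "3 questions that pertain to credibility belief, outcome expectancies, and acceptability of an OLP", put to prospective enrollees during screening. The credibility item asks about taking placebo pills and the expectancy item about this treatment. The acceptability item asks: "Based on my description of the study, are you still interested in participating". The answers are yes, no or not sure, with 48 hours and a follow-up call for those not sure. Section 3.7 repeats the item ("are you still interested in participating"), so the wording is not a slip in one place.

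Sections 3.6.1 and 3.7 add three further acceptability measures: accrual, retention and placebo pill adherence. Feasibility is the proportion who sign consent, decline, or join and drop out. Qualitative reasons are gathered from those who decline or drop out.

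The screening text in Section 3.2 lists what callers are told. This includes parking reimbursement and the payment: "They will receive up to $75.00 in the form of cash for participating in the study".

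**The concern.** The hypothesis concerns a treatment, and the item concerns a study that contains the treatment together with other things. Someone content to take a known placebo may say no because of four site visits, the agreement not to change medication, the DNA sample or the untreated period. Read as acceptability, that answer counts as rejection of the OLP. Someone indifferent to the OLP may say yes for the cash or to help research.

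Interest in joining is also close to what the sign and decline proportions already record, so feasibility and acceptability, which Section 3.6.1 treats as two outcomes, are not clearly separated. At stake is the acceptability half of the primary hypothesis. The planned ANOVA in Section 3.7, which tests whether credibility and expectancy predict acceptability, inherits the same mixture.

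An analysis plan cannot repair this, because the protocol fixes the wording of the item and a question that was not asked has no answer to analyse.

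**Working it through.** **The plan's own figure.** The protocol gives no calculation for the acceptability share. Its only sample-size figure is a total of 80 for a two-sided two-sample t-test (effect size 0.64, alpha 0.05, power 80%). This reproduces. The normal approximation gives 2(1.960 + 0.842)² / 0.64² = 38.3, so 39 per group. The exact t calculation gives 39.3, so 40 per group, with power 0.807. The present point does not depend on it.

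**What each measure can supply**

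| Measure | Object | Observed in | Pill-specific share of those screened? |
|---|---|---|---|
| Participation item | Study, OLP included | Those screened | No, mixed with study features |
| Credibility item | Placebo pills | Those screened | No, credibility and not willingness |
| Expectancy item | Treatment | Those screened | No, expected benefit |
| Accrual | Study | Enrolment count against 80 | No |
| Retention | Study | Enrollees | No |
| Adherence | Pills | Enrollees | No, not those screened |

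**Study features bundled into the answer.** These are up to $75 and parking (Section 3.2), four visits in 49 days and no change of medication (Section 3.4), a saliva sample on Day 1 (Section 3.5), and a three-week period without OLP (Section 3.1).

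**How far the share could move.** Let A be the true share of those screened who find the OLP acceptable. Let f be the fraction of these who say no because of the study, and g the fraction of the others who say yes because of the study. The measured share of yes answers is

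m = A(1 − f) + (1 − A)g.

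The documents give none of A, f or g. The assumed ranges are A from 40% to 60%, and f and g from 0 to 30%.

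False majority, with f = 0. The share m passes 50% when g exceeds (0.50 − A)/(1 − A):
- A = 40%: 0.10/0.60 = 16.7%. At g = 20%, m = 0.40 + 0.60 × 0.20 = 52%.
- A = 45%: 0.05/0.55 = 9.1%. At g = 20%, m = 0.45 + 0.55 × 0.20 = 56%.

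False failure, with g = 0. The share m falls below 50% when f exceeds (A − 0.50)/A:
- A = 60%: 0.10/0.60 = 16.7%. At f = 20%, m = 0.60 × 0.80 = 48%.
- A = 55%: 0.05/0.55 = 9.1%. At f = 20%, m = 0.55 × 0.80 = 44%.

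For A between 45% and 55%, less than 9.1% is enough. The two errors can partly cancel: A = 55%, f = 20%, g = 10% gives m = 0.44 + 0.045 = 48.5%.

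**Where the verdict is safe.** With both errors at most 30%, a true majority cannot be lost if A exceeds 0.50/0.70 = 71.4%. A false majority cannot arise if A is below (0.50 − 0.30)/0.70 = 28.6%.

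**The case against.** The strongest reply is that the protocol does not rest acceptability on this item alone. Section 3.6.1 adds accrual, retention and adherence, and Section 3.7 determines acceptability proportionally from those three. There is no arm without OLP and callers are told so, which makes a yes an agreement to receive known placebo. The credibility item is specific to the pills and covers the other half of Hypothesis 1. Interest in participating also fits the stated purpose of assessing feasibility.

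Much of this stands, and it rules out several stronger readings that a reader might infer:
- *That the acceptability part of the primary hypothesis goes unanswered.* It is answered in part, by a mixed item and three further measures. What is lacking is a pill-specific share of those screened.
- *That a false yes can never be detected.* Adherence is taken from pill counts and diaries against an anticipated 100%, and Section 3.2 ties payment to completing visits and not to taking pills. Someone who joined for the cash could show up as non-adherent. Someone who dropped out would be asked why.
- *That the question follows the cash offer.* The wording of the item suggests it, but the protocol does not state the order.
- *That a wrong verdict is likely.* Every rate in the illustration is assumed.

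The reply does not deal with the false no. That everyone receives OLP is no help with people who decline because of the study. Reasons for declining are qualitative and have no stated role in the acceptability proportion.

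**Conclusion.** The concern holds in limited form. The item labelled acceptability measures interest in a study that includes the OLP, while Hypothesis 1 needs the share of those screened who find the OLP itself acceptable. No other planned measure supplies that share, and a no caused by study burden would be misread as rejection of the OLP.

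The direction and size of the bias cannot be estimated from the protocol. If true acceptability is 40% to 60%, and only one kind of error operates, misclassifying at most about 17% of the relevant subgroup reverses a verdict at the 50% line, and about 9% is enough at 45% or 55%. If true acceptability is far from 50%, the verdict survives. The weakness is worth correcting and does not undermine the trial's other aims.

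**What to change.** Add one item to the existing screening call, where possible before payment is discussed on that call: *Would you be willing to take pills that you know are placebos to treat your fatigue?* (yes / no / not sure). Use it for the statement about the majority of those screened, and report it beside pill adherence. Keep the participation item and report it under feasibility.

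The cost is one telephone question and an IRB wording change. There are three downsides:
- A hypothetical question carries no commitment and may overstate willingness, which is why it should be read together with adherence.
- Some candidates may already know of the payment, since Section 3.2 lists it among the points used to aid recruitment. Asking first on the call therefore reduces its influence but may not remove it.
- People screened before the change will lack the item.
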